### Intervention

Both intervention arms will receive written smoking cessation materials and a series of 4 telephone-based counseling sessions and 1-3 in-person counseling sessions. Although the number, timing, and content of the counseling sessions will differ across the treatment arms, we anticipate that the total counseling contact time will be comparable, with one caveat. Participants in the SSC arm who are not interested in quitting within 30 days at the time of their baseline counseling session will not be offered additional counseling, which is consistent with most state quitlines. These participants will be informed that they may contact the program's hotline if they change their mind, at which point, counseling may either be reinstated or they will be referred to the state quit line for counseling. Participants in the SSC arm will receive 10 weeks of NRT contingent upon setting a quit date while participants in the LT-NRT arm will receive 52 weeks of NRT regardless of their immediate interest in quitting. An overview of the interventions is shown in Table 2.

## Intervention-Smoking Cessation (SSC) arm

**Written materials-SSC.** SSC participants will receive written materials designed primarily to support the counseling sessions and provide the patient with a written documentation of their treatment plan. These materials will provide information on, benefits of quitting smoking, the importance of home smoking restrictions, and strategies for a successful quit plan, including information on relapse prevention. The content of the materials are consistent with those provided to smokers that call a tobacco quitline, but have been adapted to provide more information on NRT, including information on what to do with their NRT if they are still smoking, guidance on use of combination NRT (patch plus gum or lozenge), and troubleshooting suggestions if they experience adverse symptoms from the NRT. The materials will provide a number that the participants can call 24/7 if they believe they are having problems related to their treatment. Written materials will be in their language of choice (Spanish/ English). Due to varied literacy levels, materials will be reviewed with participants by study counseling staff. (Note: Materials were revised after convening our Stakeholder Advisory Committee and our Patient Advisory Panel.)

Table 2. Comparison of intervention in SSC and LT-NRT groups

|                                                                            | SSC | LT-NRT |
|----------------------------------------------------------------------------|-----|--------|
| Written Materials                                                   |     |        |
| Cessation support                                                          | +   | +      |
| Reduction tips/replacing cigarettes with gum                               | +   | +      |
| NRT use and troubleshooting                                                | +   | +      |
| NRT adherence                                                              | +   | +      |
| Counseling                                                          |     |        |
| Counseling centered around quit date (weeks 0,1,3,6,10)                    | +   |        |
| Counseling on using NRT to cut back (weeks 0, 1, 3 & 6; Months 3, 6 and 9) |     | +      |
| NRT Guidance and troubleshooting                                           | +   | +      |
| Quit date and quit plan                                                    | ++  | +      |
| Adherence support counseling                                               | +   | ++     |
| Reduction in cigarette support                                             |     | ++     |
| NRT                                                                 |     |        |
| Combination therapy with patch & gum or lozenge                            | +   | +      |
| 12 weeks of therapy, contingent on quit date                               | +   |        |
| 52 weeks of therapy, all participants                                      |     | +      |
| + indicates that the topic is addressed                                    |     |        |
| ++ indicates that the topic is covered in more detail                      |     |        |

**Counseling-SSC.** To maximize the generalizability of the study findings, the counseling sessions for the SSC arm will emulate services provided in a typical smoking cessation program such as a state tobacco quitline. The timing, duration, and content of each counseling session will be consistent with guideline-based recommendations, and will be provided in the participants preferred language (English or Spanish). [name] will be responsible for the supervision and training on the SSC counseling protocol. [name] has extensive experience in development, training, and quality control of smoking cessation interventions, including quality monitoring for a nationwide quitline provider. Periodically, counselors will ask participants for verbal permission to audiorecord counseling sessions to demonstrate fidelity to study counseling protocols. Participants in the SSC arm will be offered up to 5 proactive counseling sessions with an in-person session at baseline and additional telephone-based sessions at weeks, 1, 3, 6 and 10 for those interested in quitting within 30 days. All counseling sessions will be delivered by a trained Tobacco Treatment Specialist. Consistent with guideline recommendations, sessions will provide basic information about smoking and successful quitting. Participants ready to set a quit date will receive practical expert support in developing a personalized plan for cessation and long-term abstinence. They will learn to recognize danger situations, develop problem-solving and coping skills, and secure social support. Counselors will encourage participants in the quit attempt, communicate caring and concern, and encourage participants to talk about the quitting process. Participants willing to set a quit date will also receive guidance on use of NRT, as outlined below. For SSC participants unwilling to make a quit attempt, the counselor will use a participant-centered approach to enhance the participant's motivation to quit as recommended in current practice guidelines. They will be informed to contact the study hotline at any time during the study, at which point they will either be referred to the state quitline or provided counseling according to the SSC protocol if still within the first 6 weeks of baseline. The participant's current tobacco-use status will guide the content of each follow-up call. If the participant is quit, the counselor will review high-risk situations, coping skills, and stress management to prevent relapse. If the participant is still smoking or has slipped, the counselor will query circumstances related to the slip and troubleshoot avoiding these situations in the future. The counselor will then use cognitive behavioral techniques to build coping skills, with the goal of helping the participant build and implement a new

quit plan. The focus will then shift to increasing motivation to make another quit attempt, including confidence building, medication use, and cessation planning. The initial face-to-face session will last approximately 30 minutes and follow-up sessions will last on average 15 minutes. Rigorous attempts will be made to reach participants for all scheduled sessions with a minimum of 3 call attempts for each scheduled session including attempts during daytime and evening hours and on alternate days.

**NRT-SC.** Consistent with the current standard of care for smoking cessation, provision of NRT will be contingent upon the participant agreeing to set a quit date. If they can identify a quit date, they will receive a 10 week supply of NRT and will be instructed to start the NRT on their chosen quit date. The dose of NRT will be adjusted to the participants smoking history as outlined in Table 3. The dose of the NRT will follow conventional treatment guidelines and is consistent with the combined NRT treatment regimens that have been shown to be effective and safe in clinical trials. Participants using NRT will be provided with both verbal and written instructions on how to use the NRT and how to avoid and manage any potential side effects. Participants will be instructed to use the nicotine patch on a daily basis even if they slip and have a cigarette. Participants will be asked to anticipate times that they typically smoke and use the gum or lozenge before deciding if they should have a cigarette. Smokers will be asked to try to consume at least 6-12 doses of gum or lozenge each day depending on their current smoking history. At each counseling call, the counselor will conduct a telephone-based assessment of the quantity of NRT used and will use this information to try to help the participant maximize their adherence to NRT.

Table 3. Dosing guide for NRT

| Smoking history                      | Dose of NRT                                   |
|--------------------------------------|-----------------------------------------------|
| Patch                         |                                               |
| < 10 cpd                             | 14 mg patch                                   |
| 10-20 cpd                            | 21 mg patch                                   |
| 21 – 39 cpd                          | 35 mg (1-21 and 1-14 mg patch)                |
| ≥40 cpd                              | 42 mg (2-21 mg patches)                       |
| Gum or lozenge                |                                               |
| When in use with combination therapy | 2 mg or 4 mg gum or lozenge every 1 – 2 hours |

### **Intervention – Long-term Guided Maintenance Therapy (LT-NRT) arm**

**Written materials-LT-NRT.** LT-NRT participants will receive the same written materials as those provided to SSC participants. This will include information on the benefits of quitting smoking and the importance of home smoking restrictions. Although the materials are identical, the smoking plan page that will be utilized in counseling and the instructions for completing it will be tailored to fit the arm, with participants in the LT-NRT group being instructed to start NRT immediately and continue its use longer term. They will receive the same information on use of combination NRT (patch plus gum or lozenge) and troubleshooting suggestions if they experience adverse symptoms from the NRT. Tips on medication adherence will be modified to address the long term nature of the treatment. As with the SSC arm, the materials will be available in either English or Spanish and will provide a number that the participants can call 24/7 if they believe they are having problems related to their treatment.

**Long-term Guided Maintenance Therapy (LT-NRT).** For the LT-NRT recipients, the counseling and NRT are integrally linked. While standard smoking cessation approaches (including our SSC comparison) address smoking cessation as a ‘one-time event’, our LT-NRT approach addresses smoking as a chronic disease that requires long term treatment. Indeed, our LT-NRT approach borrows heavily from the chronic care model of disease management and mimics techniques of patient activation and medication management used in treatment of other chronic illnesses such as diabetes and hypertension. Accordingly, our LT-NRT empowers patients with the skills to manage their NRT, reduce their cigarette consumption, and prepare themselves for quit attempts as they become ready.

Each participant in the LT-NRT arm will receive 7 counseling sessions. In contrast to the SSC group, the timing of counseling sessions will be extended to support long term adherence to NRT. Counseling sessions will occur at baseline, and weeks 1, 3, 6 and Months 3, 6 and 9. The baseline and Month 3 and 6 sessions will be face-to-face and the others will be by phone. The initial face-to-face session will last approximately 30 minutes and follow-up sessions will last on average 10-15 minutes. Rigorous attempts will be made to reach participants for all scheduled calls with a minimum of 3 call attempts for each scheduled call, including attempts during daytime and evening hours and on alternate days. Counseling will be provided in the participants preferred language (English or Spanish). [name] will be responsible for the supervision and training on the LT-NRT counseling protocol. [name] has extensive experience in development, training, and

quality control of smoking cessation interventions and has adapted interventions to specifically support medication adherence in tobacco treatment. Supervision will include the periodic review of audiotaped counseling sessions to assure counselors are adhering to protocol components.

All participants in the LT-NRT arm will be asked to begin their NRT immediately after the baseline visit using the same dosing schedule outlined in Table 3. They will receive a 3-month supply of NRT at baseline and an additional 3-month supply after the Month 3, 6 and 9 counseling sessions. (*The timing of the resupply of medications mimics the 3 month medication supply typically used in healthcare settings for other chronic diseases – thus enhancing the potential for generalizability and adoption of the proposed intervention.*) The baseline visit will focus on the use of NRT, NRT adherence, and how NRT can be used to support smoking reduction. Smokers interested in making a quit attempt will be given cessation advice and supportive counseling as described in the written support materials. LT-NRT participants who continue to smoke will be asked to continue their NRT regardless of their current level of smoking and will be given supportive advice on maximizing adherence with NRT. LT-NRT participants who have quit smoking will be asked to continue NRT for a minimum of 6 months after they no longer experience smoking-related urges. If they have been abstinent for 6 months and no longer have urges to smoke, they will be provided a regimen for tapering their NRT dose with strict instructions for resuming the full dose if they have a slip or if smoking-related urges recur. LT-NRT participants will also receive adherence support counseling. Since some of the LT-NRT participants will not be ready for extensive counseling on quitting, the adherence support counseling will be particularly important. Adherence support counseling has been previously tested by our group and will assist participants in identifying problems remembering to take their medication and help them develop strategies for remembering (e.g., timing doses with routine activities of daily living, posting reminders, setting alarms). Adherence support counseling will reinforce the continued use of NRT as one of the single best strategies for quitting or reducing smoking. This counseling will follow a semi-structured format that assesses smoking status and medication use, probes for difficulties participants are having with their medication, assists participants in problem-solving around issues they are having remembering to take their medications, and offers suggestions for dealing with self-reported side effects. Notably this counseling approach has resulted in high rates of adherence to smoking cessation medication (86%, biochemically verified). In the present study, we will not be able to biochemically verify adherence to NRT since nicotine in the blood could reflect either adherence to the treatment or continued smoking. Instead, adherence will be assessed using a 3-day recall of medication use. This approach is considered the gold standard when biochemical verification of adherence is not possible and in our own work has been validated with high sensitivity and specificity against medication blood levels.

#### **Safety monitoring.**

As with prior studies on combined NRT and use of NRT in continuing smokers, we anticipate few side effects with the treatment; however, as noted above, participants in both treatment arms will be prompted to report side effects at each contact and will be given the toll-free study phone number to report any adverse events at interim time points. Issues needing medical attention will be referred to [name]. We will follow NIH guidelines for reporting adverse events to the Human Subjects Committee, and address any unforeseen problems with our Data and Safety Monitoring Board. The DSMB will also receive quarterly reports to assure that side effects are not occurring at an unusually high rate.

In addition, if participants consent, we will inform their physician about their patient's participation in the study, providing them with basic details on the study along with our contact information so that they can reach us if they have questions or concerns.

#### **Study visits and data collection methods**

Trained research assistants will conduct assessments at baseline and 3, 6, and 12 months post-enrollment. Participants will receive a \$50 ClinCard for each assessment completed, which is similar to a prepaid credit card and can be used almost everywhere that credit cards are accepted. Compensation will not be contingent on smoking status. To help remove transportation barriers for participants without transportation who live within a reasonable distance from one of our site locations, we will offer to provide cab vouchers for participants to get to and from their appointments. In order to offset this cost, participants must be willing to have their payment for that visit reduced to \$30. To maximize retention, participants will be asked at the

baseline visit to provide contact information to facilitate follow-up: address, email, two telephone numbers if possible, and information for an alternate contact person. Reminder post cards and multiple calls will be used to maximize attendance at follow-up visits. To facilitate follow-up, staff will keep flexible hours providing opportunities for follow-up during evening and weekend hours. Follow-up will be conducted primarily at one of our two Clinical Research Units – both of which have easy parking within 100 feet of the door. To further facilitate follow-up, research assistants will also try to time follow-up assessments so that they can be coordinated with medical visits at KUMC.

## Measures

**Outcome measures.** Our selection of outcomes was derived from scientific expert consensus and informed by input from our stakeholders and smokers with COPD. (Table 4) The primary outcome is biochemically verified 7-day point prevalence smoking abstinence defined as no cigarettes (not even a puff) for the previous 7 days at month 12. Biochemical validation will be based on expired CO, consistent with consensus statements from the Society for Research on Nicotine and Tobacco (SRNT). For those participants who have reported they have quit smoking and who are unable to be verified in this way, we will obtain verbal permission and contact information for a household member or other regular contact to provide proxy validation.

Secondary outcomes are 6 month sustained abstinence (biochemically verified), number of quit attempts, average CPD over the year of the study, and cumulative exposure to CO and NNAL. We will examine relapse rates 3 months after the conclusion of the study for participants who report they have quit smoking at the 12-month assessment. Clinical outcomes include both objective and subjective measures of respiratory function based on the measured FEV1 (as a percent of predicted) and the COPD Assessment Test.

We will also track both respiratory and cardiac clinical events. This will be done by self-report of intercurrent emergency department visits and hospitalizations at each follow-up visit. We will validate both the occurrence and the nature of these self-reported clinical events by blinded physician review of medical records.

Although our primary outcome, biochemically verified smoking cessation is a standard outcome for smoking cessation studies and has been endorsed by scientific experts; other outcomes included in this study have been driven by our patients and stakeholders. Our patients not only want to quit smoking, but want to feel better and spend less time in the hospital. They also would like to see that they are reducing their exposure to cancer-causing chemicals. Our stakeholders are very interested in the impact of the intervention on cessation and clinical events. These additional outcomes make this study relatively unique among smoking cessation studies. These additional outcomes are well aligned with our choice of focusing on participants with COPD. To date no controlled clinical trials have tested long term NRT in patients with COPD. Nevertheless, by focusing on patients with COPD, we have a much better chance of detecting meaningful differences in clinical outcomes associated with the intervention. Our study will also employ objective markers of smoke exposure (CO and NNAL). With rare exceptions, prior studies of long term NRT that looked at reduction in smoking used

Table 4. Key outcome measures

| Construct                                          | Measure (assessment timepoint)                                                                                                                                                                                                                                       |
|----------------------------------------------------|----------------------------------------------------------------------------------------------------------------------------------------------------------------------------------------------------------------------------------------------------------------------|
| Smoking outcomes                                   |                                                                                                                                                                                                                                                                      |
| Smoking abstinence at 12 months*                   | 7-day point prevalence abstinence, confirmed by exhaled CO or proxy validation (Mo 12)                                                                                                                                                                               |
| 6 month sustained smoking abstinence               | Self reported 6 month abstinence at 12 month confirmed by exhaled CO or proxy validation (Mo 6 & 12)                                                                                                                                                                 |
| Quit attempts                                      | Cumulative number of self-reported quit attempts lasting at least 24 hours (baseline, Mo 3, 6 & 12)                                                                                                                                                                  |
| Average CPD                                        | Average number of CPD (baseline, Mo 3, 6 & 12)                                                                                                                                                                                                                       |
| Smoke exposure                                     |                                                                                                                                                                                                                                                                      |
| Cumulative CO exposure over 12 months              | Expired CO will be measured at each follow-up visit allowing an assessment of cumulative CO exposure. (baseline, Mo 3, 6 & 12)                                                                                                                                       |
| NNAL exposure over 12 months                       | Urinary NNAL will be measured at each follow-up visit allowing an assessment of cumulative NNAL exposure. (baseline, Mo 3, 6 & 12)                                                                                                                                   |
| Clinical outcomes                                  |                                                                                                                                                                                                                                                                      |
| Respiratory function                               | Simple spirometry will be performed at baseline and at the final follow-up visit. (baseline, Mo12)                                                                                                                                                                   |
| Respiratory symptoms                               | Respiratory symptoms will be measured using the COPD Assessment Test (baseline, Mo 3, 6 & 12)                                                                                                                                                                        |
| Respiratory-related hospitalizations and ED visits | Intercurrent hospitalizations and emergency department visits will be assessed at each follow-up visit. Patients will be asked to classify the event as related to their heart or breathing. These will be validated by blinded physician review of medical records. |
| Cardiac-related hospitalizations and ED visits     |                                                                                                                                                                                                                                                                      |

\*Primary outcome

self-report of CPD or they looked at nicotine metabolites (i.e. cotinine). Self-report of CPD is highly problematic, because even if smokers really do reduce the number of cigarettes they smoker, they tend to smoke those cigarettes more efficiently, and cotinine measurements are confounded by the use of therapeutic NRT. Our measures of CO and NNAL will allow us to have objective measure of actual smoke exposure. The NNAL is particularly relevant to our patients who would like to reduce exposure to carcinogens. NNAL (4-(methylnitrosamino)-1-(3)pyridyl-1-butanol) is a pulmonary carcinogen and metabolite of 4-(methylnitrosamino)-1-(3)pyridyl-1-butanone (NNK), a tobacco-specific nitrosamine related to the development of lung cancer. NNAL assessed in urine is highly correlated with smoke-related tobacco exposure.

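### The primary and sustained-abstinence outcomes are labelled biochemically verified, but Table 4 also counts quitters confirmed only by a proxy, and no rule makes a CO reading that indicates smoking decisive.

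*Protocol*

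**What the plan says.** Protocol, Measures, Outcome measures: "The primary outcome is biochemically verified 7-day point prevalence smoking abstinence" at month 12, and "Biochemical validation will be based on expired CO". The same paragraph then opens a second route. For self-reported quitters "who are unable to be verified in this way, we will obtain verbal permission and contact information for a household member" or another regular contact, who then serves as the proxy. The next paragraph of that section attaches the biochemical label to 6-month sustained abstinence too. The text introducing Table 4 repeats the label for the primary outcome, with no mention of proxies.

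Table 4 gives the operational definitions. The starred primary outcome is "7-day point prevalence abstinence, confirmed by exhaled CO or proxy validation (Mo 12"). Sustained abstinence is likewise "confirmed by exhaled CO or proxy validation (Mo 6 & 12").

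The Analytical Plan compares verified 7-day abstinence at Month 12 with a chi-square test, 199 per arm, and does not say there which kind of verification is meant.

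**The concern.** There are two separate faults.

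**Label against definition.** A statement from a household member or acquaintance is not a biochemical test. A reader of the results would take the abstinence rates as CO-confirmed when some of the counted quitters may have no CO confirmation at all.

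**No order of precedence.** The trigger for the proxy route is being unable to be verified by CO. That phrase fits a participant who gave no breath sample. It can also be read to fit one whose sample did not confirm abstinence. Table 4 joins the two methods with a plain or. Staff at the Month 12 visit could apply either reading and still be following the protocol.

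The participants know their arm (52 weeks of NRT against 10 weeks contingent on a quit date) and supply the proxy's contact details. False confirmations at the same rate in both arms would dilute the contrast. At different rates they would bias it. Few quitters are expected, about 20 per arm at the planned 10%, so a handful of proxy cases can matter.

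**Working it through.** **Step 1: set the texts side by side.**

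| Place in protocol | Primary outcome | Sustained abstinence |
|---|---|---|
| Measures, Outcome measures | biochemically verified, based on expired CO; proxy if CO verification is not possible | biochemically verified |
| Measures, text introducing Table 4 | biochemically verified | not mentioned |
| Measures, Table 4 | CO or proxy | CO or proxy |
| Analytical Plan | verified | no verification method named |

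The biochemical label and the CO-or-proxy definition cannot both describe the same count. Nothing in the protocol limits the proxy to participants without a CO result, and nothing says that a CO reading indicating smoking settles the matter.

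**Step 2: reproduce the plan's own figure.** Inputs from the Analytical Plan: 10% in SSC, a 2-fold increase (so 20% in LT-NRT), 80% power, 5% type I error (taken as two-sided). With pooled variance under the null and no continuity correction:

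n = [1.960 × √(2 × 0.15 × 0.85) + 0.842 × √(0.10 × 0.90 + 0.20 × 0.80)]² / 0.10² = (0.990 + 0.421)² / 0.01 = 199 per arm.

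The stated 199 is reproduced. The sample size is not in question.

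**Step 3: illustrate the effect of false confirmations.** The false-confirmation rates below are assumptions; the documents give none. The method is exact enumeration. Every pair of counts (0 to 199 in each arm) is weighted by its binomial probabilities, and the probabilities of the pairs where the uncorrected chi-square has two-sided p < 0.05 are summed.

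*Same error in both arms, true rates 10% and 20%:*

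- No false confirmations, 10% v 20%: power 80.9%.
- Two points added to each arm, 12% v 22%: power 76.7%.

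*Net excess in one arm, no true difference, 10% abstinence in both:*

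| Excess | People (of 199) | Counted rates | Chance of p < 0.05 |
|---|---|---|---|
| 0 points | 0 | 10% v 10% | about 5% |
| 1 point | 0.01 × 199 ≈ 2 | 10% v 11% | 6.0% |
| 3 points | 0.03 × 199 ≈ 6 | 10% v 13% | 15.2% |

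Starting instead from 12% in both arms, a 3-point excess gives 14.1%.

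**Step 4: put the scale in view.** At 10% there are 0.10 × 199 ≈ 20 quitters per arm. An excess of 6 false confirmations is 6/20 = 30% of that number, and it is net of any in the other arm. Each such person must report having quit, lack CO confirmation, and have a proxy who is wrong. An excess of 1 point (2 people) is easier to imagine and leaves the error rate close to nominal.

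**The case against.** The proxy route is not hidden. It follows the definition closely in the Outcome measures text, it is written into Table 4, and the Analytical Plan says verified rather than biochemically verified. This stands as far as it goes: the endpoint is a disclosed composite with the wrong name. Disclosure does not make the name right, and it does not supply the missing precedence rule.

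A reader might infer three stronger points that the documents do not support.

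- **That the protocol plans for a proxy to rescue a failed CO test.** The ordinary sense of being unable to be verified may well be that no sample could be obtained. No text says a participant with a high reading goes to a proxy. The wording permits it; that is all.
- **That proxy use will be unequal, because SSC participants not ready to quit are cut off after baseline.** They are not. The Intervention section lets them call the hotline, after which counselling may be reinstated or they are referred to the state quitline. The Counseling-SSC section offers the SSC sessions if they call within the first 6 weeks. Both arms also share the same 3-, 6- and 12-month assessments with the same payment and transport help (Study visits and data collection methods). Unequal proxy use is possible, in either direction, but is not shown.
- **That CO-only abstinence must become the primary outcome.** That is a debatable choice. The Analytical Plan first analyses the data ignoring missing values, so a CO-only primary would have to say whether a self-reported quitter with no CO result is missing or smoking. The first option drops quitters who cannot attend; the second misclassifies true quitters.

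A sensitivity analysis and the CO cut-off itself may sit in a statistical analysis plan that is not shown, so their absence alone is not the fault. The contradictory definition and the missing precedence rule are in the protocol.

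**Conclusion.** The point holds on the text. Two outcomes, one of them primary, carry a biochemical label that their Table 4 definition does not meet, and the protocol leaves open whether a proxy can overrule a CO reading that indicates smoking. Followed as written, the plan would report any proxy-only quitters as biochemically verified.

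The size is unknown. The figures of about 6% and 15% rejection, and the fall in power from 81% to 77%, rest wholly on assumed false-confirmation rates. They show that a few cases could matter with so few quitters expected; they do not estimate the trial's actual error rate. The change is worth making because it is cheap and removes the doubt before anyone knows how many proxy cases there are.

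**What to change.** In the Outcome measures text, the paragraph introducing Table 4, and Table 4 itself:

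1. Limit the proxy route to self-reported quitters with no CO result, and state that a CO reading above the pre-set cut-off counts as smoking whatever the proxy says.
2. Rename both the primary outcome and 6-month sustained abstinence as CO- or proxy-verified, so that label and definition agree.
3. Report the number of proxy-only confirmations per arm, and add a CO-only sensitivity analysis in which self-reported quitters without a CO result count as smoking.

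The cost is a few changes of wording and one extra analysis. In that analysis a few true quitters who could not give a CO sample will be counted as smokers. The sample size does not change.
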